### Statistical Analysis

All analysis will be conducted in Stata version 15 (StataCorp LP) using the principles of intention-to-treat analysis. We will use descriptive statistics to characterize the groups at baseline. The intention-to-treat analysis for this study will include all participants, including those who are not fully compliant and those with missing outcome data. The primary outcome will be the change in total body lean soft tissue mass. Secondary outcomes include changes in physical fitness, muscle strength, physical function, and blood biomarkers. The primary analysis will compare the primary and secondary outcomes resulting from the intervention, using linear mixed models to model outcomes at T1, T2, and T3 adjusted for baseline values. Standard mixed-model diagnostics will be performed. Group differences will be presented in the form of mean differences for continuous outcomes and an odds ratio for binary outcomes, with their associated 95% confidence intervals.

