#### High-Intensity Interval Training Group

The intervention includes a 40-week RCT of HIART. The 40-week intervention involves 20 weeks of training followed by a 20-week follow-up. Each training session will start with a warm-up, followed by HIART, and finishing with a cooldown. HIART involves 3 phases, as follows.

The first is a *power phase* consisting of 2 whole-body exercises, performed for 20 seconds each with maximum intensity, followed by 10 seconds of rest and repeated 8 times. Between each whole-body exercise will be a 1-minute rest. Exercises include jumping jacks, skaters, burpees, and numerous other calisthenics varied by session.

The second is a *cycling phase*, which will be based on the 3-minute all-out protocol as proposed by Gillen et al [26]. We will use stationary spin bikes for this phase (4000GT Spin Bike; AeroSpin). The cycling phase will begin with a 2-minute warm-up, followed by 2 times 4 sets of 20-second all-out sprints interspersed with a 1-minute recovery, followed by a 2-minute cooldown. Participants will be encouraged to increase wattage when appropriate.

Third is a *resistance phase* consisting of 2 resistance exercises with or without free weights. The resistance exercises will target major muscle groups. Exercises will be performed as supersets (antagonistic muscle groups), compound sets (same muscle group[s]), or staggered sets (noncompeting muscle groups; eg, upper and lower body). Participants will perform each exercise 8 times for 20 seconds, followed by a 10-second rest.

Participants will complete all exercises as a circuit with a 1-minute rest between exercises. Training load will be self-selected, but participants will be encouraged to choose a weight or resistance that will ensure that their HR reaches 85% of maximum HR during the high-intensity peaks and does not drop below 60% of maximum HR during the low-intensity periods in the power and cycling phases. All training sessions will be group based, with a maximum of 9 people in each group. Experienced staff with extensive background in group fitness will lead every exercise class. At the end of the 20-week exercise intervention, participants will be given access to the 20-week home program to complete sessions at home.

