### Sample Size

Based on a standard deviation of 1.9 kg and an effect size *f* of 0.39 (obtained from previous literature [37]), our study has 95% power using a 2-sided 5% level of significance to detect clinically meaningful differences in lean soft tissue mass of 1.5 kg between the intervention and the control group with 35 participants per group. We will aim to recruit 84 participants (42 per group), which allows for 15% dropout or unusable data.

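### HIART is delivered in groups of at most 9, but the sample size allows nothing for within-group correlation in that arm and the stated model does not mention it

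*Protocol article*

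**What the plan says.** Participants are randomised individually, 1:1 (Blinding, Randomization Methods, and Allocation Concealment). In the HIART arm, "All training sessions will be group based, with a maximum of 9 people in each group", and staff lead every class (High-Intensity Interval Training Group). The Adherence section counts group participation among the strategies to improve adherence. It also lets participants reschedule to another session, and it monitors participation with attendance checklists. Controls receive one 60-minute group education session. After week 20 they are offered 3 weeks of supervised exercise (Control Group).

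The Sample Size section states that "our study has 95% power" for a 1.5 kg difference in lean mass, taking an SD of 1.9 kg, a two-sided 5% test and 35 people in each arm. Its only inflation is this: "We will aim to recruit 84 participants (42 per group), which allows for 15% dropout or unusable data". It gives no ICC, design effect or class size.

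The Statistical Analysis section compares groups "using linear mixed models to model outcomes at T1, T2, and T3 adjusted for baseline values". It specifies no random effects, so it neither includes nor excludes one for training class.

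**The concern.** This is a partially nested design. For 20 weeks one arm trains in a small number of groups, and the other arm has a single group contact before T2. People who train together share sessions, exercise selection, encouragement and attendance habits, so their outcomes may be alike for reasons that individual randomisation does not remove. The variance of the HIART mean then contains a between-class part that shrinks with the number of classes and not with the number of people.

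If the analysis ignores that part, the standard error of the HIART-control difference is too small, the 95% interval covers less than 95%, and the test rejects more often than 5% under the null. A power figure computed as if all participants were independent is then too high.

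**Working it through.** **Inputs from the article.** SD 1.9 kg; difference 1.5 kg; two-sided 5%; 35 evaluable per arm, 42 recruited per arm; at most 9 per training group.

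**Assumptions.** The article gives no class ICC, so I take 0.01 to 0.05, and 0.10 as an outer value. Classes are 9/9/9/8 with stable membership. The control arm is unclustered. The outcome is a single comparison with the planned SD.

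**1. The plan's own figures.**
- Dropout: 35/(1 − 0.15) = 41.2, rounded up to 42. This reproduces, and it leaves no allowance for clustering.
- Power: d = 1.5/1.9 = 0.789, so f = 0.789/2 = 0.395, in line with the stated 0.39. The standard error is 1.9 × √(2/35) = 0.454 kg and the noncentrality is 1.5/0.454 = 3.30. Two-sided 5% power is 90.2% by the noncentral t (91.0% by the normal approximation).
- The stated 95% does not reproduce. A one-sided 5% test with the same inputs gives 94.8% (t) or 95.1% (normal). The 4 to 5 point gap exists before any clustering.

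**2. Number of classes.** 35/9 = 3.9 and 42/9 = 4.7, so at least 4 and 5 classes.

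**3. Design effect, HIART arm only.** The size-weighted mean class size is m = (3 × 9² + 8²)/35 = 307/35 = 8.77.
- DE = 1 + (m − 1) × ICC = 1 + 7.77 × ICC
- True SE / independent SE = √((1 + DE)/2)
- Power: noncentral t with noncentrality 3.30 divided by that ratio

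| ICC | DE | SE ratio | Type I error, class ignored | Power, design effect only |
|---|---|---|---|---|
| 0 | 1.00 | 1.00 | 5.0% | 90.2% |
| 0.01 | 1.08 | 1.02 | 5.3–5.4% | 89.1% |
| 0.02 | 1.16 | 1.04 | 5.8–5.9% | 88.0% |
| 0.05 | 1.39 | 1.09 | 7.2–7.5% | 84.6% |
| 0.10 | 1.78 | 1.18 | 9.5–9.8% | 78.9% |

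The type I ranges span the closed-form value and simulations of the ordinary t-test. At ICC 0.05 the closed form gives 7.2%, so a nominal 95% interval covers about 93%.

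**4. If all 42 per arm were evaluable.** With classes of 9/9/8/8/8, power is 94.7% at ICC 0 and 90.7% at ICC 0.05.

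**5. Cost of a test that models class.** A partially nested test with Satterthwaite degrees of freedom, simulated at 35 per arm in 4 classes, has power of 82.3%, 80.4%, 78.9% and 73.7% at ICC 0, 0.01, 0.02 and 0.05. Its type I error is 3.5% to 4.8%, so it is somewhat conservative. At ICC 0.05 the total fall is 90.2 − 73.7 = 16.5 points. Of this, 90.2 − 82.3 = 7.9 points arise at ICC 0, so they come from the few degrees of freedom and not from correlation.

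**The case against.** **The model may already handle class.** A linear mixed model can carry a class effect, and an article commonly leaves the random-effects structure to a full protocol or analysis plan, neither of which is shown. This stands. A reader might infer that the planned model treats participants as independent, but the article does not say so. It does not reach the Sample Size section, which gives a complete calculation whose only inflation is for dropout.

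**Classes may not be stable.** The limit of 9 could be a session capacity. Fixed membership is not stated, rescheduling is allowed, training load is self-selected and the number of leaders is not given. This also stands, and it points to a small ICC. At 0.01 to 0.02 the design-effect loss is only 1 to 2 points of power.

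**The harm is conditional.** At ICC 0 nothing is lost. A reader might conclude that the interval is too narrow, but the documents support that only if the ICC is above zero and class is left out of the model.

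**The remedy has its own price.** A reader might also take the fall from 90% to about 74% at ICC 0.05 as the effect of clustering. Nearly half of it is the price of the small-degrees-of-freedom test.

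**Conclusion.** The point holds in conditional form. The design makes correlation within training group possible in the HIART arm only, the sample size allows nothing for it, and the stated model does not mention it. If the class ICC is above zero and the analysis omits class, the interval is too narrow; the planned power is overstated at any ICC above zero.

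Over an assumed ICC of 0.01 to 0.05 the size is modest: a standard error understated by a factor of 1.02 to 1.09, type I error of about 5.3% to 7.5%, and power of 89.1% to 84.6%. The low end is the more likely, given rescheduling. These figures rest on stable classes of about 9, 35 evaluable per arm and an unclustered control arm.

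Most of the gap between the stated 95% and these values is not clustering. The design has about 90% power at two-sided 5% even at ICC 0.

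**What to change.** 1. **Sample Size.** Replace the 95% with power at two-sided 5% and 35 per arm of about 90% at ICC 0, 88% at ICC 0.02 and 85% at ICC 0.05. State that these use the design effect only and that the ICCs are assumed. Data collection is reported as complete, so this corrects the justification and does not change the design.

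2. **Statistical Analysis.** Prespecify a partially nested analysis of the T2 comparison: a random effect for usual training class in the HIART arm only, each control as their own cluster, and Satterthwaite or Kenward-Roger degrees of freedom. Report it beside the model without the class effect, with the estimated class ICC. Limit it to T2, because controls are offered supervised exercise before T3.

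3. **Conditions.** The analysis is possible only if the attendance records show which session each person attended, so that usual class can be defined as the one attended most often. The article says only that checklists monitor participation. A class code present in one arm would reveal allocation, so it must be handled in a way that keeps the analyst masked.

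**Cost.** No new participants or measurements, and a few lines of model code. The interval will be wider, and a class variance estimated from 4 or 5 classes is imprecise. The small-degrees-of-freedom test has only about 82% power even at ICC 0; the plan should state this openly and not present it as an effect of clustering.

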### Blinding, Randomization Methods, and Allocation Concealment

Figure 1 shows the study flow. Following the screening assessments eligible participants will be randomly allocated to either a control group or HIART group at a 1:1 allocation ratio. Stratified block randomization allocation sequence will be generated in REDCap (REDCap Consortium) and will be used to automatically randomly allocate participants to groups of equal sample size, stratified by sex, age and BMI. The block sizes and allocation sequence will not be disclosed to ensure concealment. The investigator collecting the data will feed data into the computer in separate datasheets, which will be anonymized by a different investigator, to ensure that all other investigators, including lab technicians, cardiologist and the primary investigators remain blinded to the treatment allocation. Statistical analysis will be performed using the anonymized datasets to ensure masking to treatment allocation.

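### Allocation is stratified by sex, age and BMI but the stated model adjusts only for baseline values; if these factors are prognostic beyond baseline, inference is mildly conservative

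*Protocol article*

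**What the plan says.** The section on blinding, randomisation and concealment has participants "randomly allocated to either a control group or HIART group at a 1:1 allocation ratio", using a stratified block sequence that "will be used to automatically randomly allocate participants to groups of equal sample size, stratified by sex, age and BMI".

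The Statistical Analysis section defines the primary outcome: "The primary outcome will be the change in total body lean soft tissue mass". It compares primary and secondary outcomes "using linear mixed models to model outcomes at T1, T2, and T3 adjusted for baseline values". Sex, age and BMI are not named as model terms anywhere in the article, nor does it say that they will be left out.

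The Sample Size section gives the only planning figures: "Based on a standard deviation of 1.9 kg", a target of "clinically meaningful differences in lean soft tissue mass of 1.5 kg", and 35 participants per group. It mentions no covariate adjustment.

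**The concern.** Stratified allocation makes the arms more alike on the stratifying factors than simple randomisation would. The treatment contrast then varies less from one randomisation to the next, to the extent that those factors predict the outcome. A model without them leaves the between-stratum variation in its residual, so its standard error does not reflect the reduction. Confidence intervals come out wider than the design warrants, and p-values larger.

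At stake is efficiency in a small trial, together with agreement between design and analysis. The same model serves the secondary outcomes (fitness, muscle strength, physical function, biomarkers), where sex in particular could remain prognostic after baseline adjustment. The article gives no figure for that.

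**Working it through.** **Inputs from the article.** SD 1.9 kg, difference 1.5 kg, 35 per group, two-sided 5%, stated power 95% (Sample Size); 82 enrolled (Results).

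**Assumptions.** R² is the share of the variance left after baseline adjustment that sex, age and BMI explain. The article gives no value, so I use 0 to 0.20. I treat 1.9 kg as the residual SD of a model with baseline only, and consider one between-group contrast at one time point.

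**Step 1: the plan's own figure.** The standard error is 1.9 × √(2/35) = 0.454 kg. Two-sided power is Φ(1.5/0.454 − 1.96) = Φ(1.343) = 91.0% (noncentral t: about 90.3%), not the stated 95%. A one-sided 5% test gives 95.1%. A repeated-measures calculation can also come close to 95%, but only under correlations that the article does not state. That discrepancy is a separate matter. I use 91.0% as the starting point because it follows from the printed inputs.

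**Step 2: effect of leaving the strata out.** Under stratified allocation:

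- SE reported without strata: m = 1.9 × √(2/n)
- True SE: t = 1.9 × √(1 − R²) × √(2/n)
- Overstatement: m/t = 1/√(1 − R²)
- Type I error without strata: 2 × [1 − Φ(1.96 × m/t)]
- Power without strata: Φ((1.5 − 1.96m)/t)
- Power with strata: Φ(1.5/t − 1.96)

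| R² | SE reported / true (kg) | Overstated by | Type I error, strata omitted | Power omitted | Power included | Gain (points) |
|---|---|---|---|---|---|---|
| 0 | 0.454 / 0.454 | 0% | 5.0% | 91.0% | 91.0% | 0 |
| 0.05 | 0.454 / 0.443 | 2.6% | 4.4% | 91.6% | 92.3% | 0.7 |
| 0.10 | 0.454 / 0.431 | 5.4% | 3.9% | 92.2% | 93.6% | 1.4 |
| 0.20 | 0.454 / 0.406 | 11.8% | 2.8% | 93.3% | 95.8% | 2.5 |

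Worked line for R² = 0.10: t = 0.454 × √0.90 = 0.431. Omitted: (1.5 − 1.96 × 0.454)/0.431 = 1.415, so 92.2%. Included: 1.5/0.431 − 1.96 = 1.521, so 93.6%.

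**Step 3: simulation.** The set-up was 70 participants, three two-level factors giving eight strata, permuted blocks of four, covariance analysis with and without the factors, and 6,000 replicates. Block size and cut-points are assumptions. Power without and with the factors:

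- R² = 0: 90.0% and 89.4%
- R² = 0.10: 91.4% and 92.5%
- R² = 0.20: 91.5% and 94.7%

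The direction agrees. At R² = 0.20 the simulated gain is 3.2 points rather than 2.5. Incomplete blocks leave some imbalance, so the model without strata benefits less from stratification than the formula assumes. At R² = 0 the extra terms cost about half a point. Simulated type I error without the factors was 4.8%, 4.4% and 3.2% at R² of 0, 0.10 and 0.20.

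**Step 4: the enrolled number.** If all 82 contribute and split evenly (82/2 = 41 per group), the same formulas give 95.6% and 96.5% at R² = 0.10, and 96.5% and 97.9% at R² = 0.20. The gains are 0.9 and about 1.5 points.

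**The case against.** The strongest reply is that this is a condensed article, the analysis plan is not shown, and model terms are commonly settled there. Silence about the strata is not a decision to exclude them. That stands as far as it goes: the article does not prove that the final analysis omits them. But it does not leave adjustment open either. It states an adjustment set, and that set, read naturally, does not contain the factors.

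The second reply is that the loss may be close to nil. Baseline lean mass is already in the model and plausibly carries much of the information in sex and BMI. Entry is restricted to ages 40 to 50, which limits what age can add, and the sex-specific lean-mass cut-offs narrow body composition within each sex. This stands for the primary outcome, and is why the range must include zero.

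Three stronger readings are tempting, and the documents do not support them.

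- A reader might infer that standard errors are certainly too large and power certainly lost. That needs an R² above zero, which the article does not give.
- A reader might compare 91.0% with the adjusted 92.3% to 95.8% and call the whole difference the gain. That is the wrong comparator. Under stratified allocation the unadjusted analysis also benefits, reaching 91.6% to 93.3%, so the like-for-like gain is 0.7 to 2.5 points at R² of 0.05 to 0.20.
- A reader might see a threat to validity. There is none for the mean differences: the error is on the conservative side, and in the formula above power without the strata never falls below the 91.0% implied by the plan's own inputs.

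**Conclusion.** The point holds in a limited form. Randomisation uses sex, age and BMI; the stated model does not. If the factors carry prognostic information beyond baseline, intervals are somewhat too wide and tests conservative, with no bias in mean differences and type I error at or below 5%. For an assumed R² of 0 to 0.20 and 35 per group, the standard error is overstated by 0 to 12% and the type I error is 5.0% down to 2.8%. The power forgone is about 0 to 2.5 points by normal approximation, slightly more at the top of the range in simulation, and less with 41 per group.

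The mismatch and the direction are firm. The size rests on an R² that the article does not supply and that may be near zero for lean mass. The figures apply to continuous outcomes. Severity is minor: the reason to act is that analysing by the factors used in allocation costs almost nothing.

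**What to change.** State in the analysis plan that sex, age and BMI enter as fixed effects, alongside the baseline value of the outcome, in the primary model and every secondary model. Age and BMI can be continuous. If any outcome is analysed as binary, say that the odds ratio is conditional on these covariates, because adjustment changes what an odds ratio estimates.

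The Results section reports data collection complete and analysis underway, so the change should be dated and declared before the masked datasets are linked to allocation. Its justification is the design, not the data.

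The cost is one sentence and about 3 degrees of freedom. The variables were all needed to randomise. The worst case is about half a point of power if the factors explain nothing.

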## Results

We obtained ethical approval for this study from The University of Otago Human Ethics Committee on December 10, 2018. The project is supported by a University of Otago Research Grant and a Dunedin School of Medicine Dean’s Bequest Fund (January 2019 to March 2020). Patient recruitment started on February 11, 2019 and was completed on May 14, 2019. Data collection started on February 25, 2019 and was completed on February 28, 2020. We enrolled 82 participants. Data analysis is underway and we expect to publish results in January 2021.

## Discussion

HIART may have substantial benefit, including improving body composition, strength, and fitness, in middle-aged adults with low lean soft tissue mass. HIART is a time-efficient form of exercise, enabling busy middle-aged adults to meet physical activity recommendations while maximizing training results.

This RCT is rigorously designed, allowing conclusions to be formed about the acceptability and effectiveness of a supervised, group-based HIART intervention in middle-aged adults with low lean soft tissue mass. The findings can inform the development of future prevention-focused interventions aimed at counteracting the high prevalence of sarcopenia in the aging population.

## Abbreviations

ALMI: appendicular lean soft tissue mass index
DXA: dual energy X-ray absorptiometry
ECG: electrocardiogram
ESES: Exercise Self-Efficacy Scale
HIART: high-intensity interval aerobic resistance training
HIIT: high-intensity interval training
HR: heart rate
LAQ: Lifestyle Appraisal Questionnaire
PACES: Physical Activity Enjoyment Scale
RCT: randomized controlled trial
SF-12: 12-item Short Form Health Survey
O_2_max: maximum oxygen consumption
